## 10.9 Criteria for exclusion from analysis

Safety data analysis will be performed on all subjects who received at least one dose of study vaccine/virosomes, and for whom at least one set of safety follow-up data is available (i.e. safety population).

Subjects will be included in the final analysis of immunogenicity if they fulfill the following criteria (i.e. per protocol analysis):

- All inclusion/exclusion criteria were respected
- They received the vaccine they were randomized to receive
- They received a second dose of the vaccine
- Allowed intervals between injections were respected
- Allowed intervals between blood sampling schedules were respected
- No forbidden vaccine or concomitant medication was taken

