| SAFETY                         |                                                   | 
 
Occurrence of adverse events: self-assessment of local and systemic reactions for 4 days after each vaccination (diary) as well as assessment by investigator during 30 minutes after each vaccination and 2 (+1) days as well as 7 (+2) days after each vaccination.
 
Occurrence of clinically significant hematological and biochemical abnormalities (hematological and biochemical analysis will be carried out at the screening visit (baseline), 7 (+2) and 21 (+5) days after each vaccination).
 
Significant reduction of health status compared to baseline (as assessed by investigator at baseline, i.e. prior to 1st vaccination, during 30 minutes after each vaccination and 21 (+5) days after each vaccination).
 
                                                                                                                                                                                                                                                                                                                                                                                                                                                                                                                                                                                                                                                                                                                                                                                                                                                                                                                                        |

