### **4.3 Exclusion criteria**

The following criteria should be checked at the time of study entry. If any apply at the time of study entry, the subject must not be included in the study:

1. Use of any investigational or non-registered drug or vaccine within 30 days preceding the first dose of study vaccine, or planned use during the study period and safety follow-up.
2. Chronic administration (defined as more than 14 days) of immunosuppressants or other immune-modifying drugs within six months prior to the first vaccine dose. (For corticosteroids, this will mean prednisone, or equivalent,  $\geq 0.5$  mg/kg/day. Inhaled and topical steroids are allowed.)
3. Any chronic drug therapy to be continued during the study period.
4. Longterm residency in a malaria endemic area in the past
5. Visit to malaria endemic area within 12 months previous to study start
6. Intention to travel to malaria endemic area during the study period
7. History of clinical malaria
8. Any confirmed or suspected acquired immunosuppressive or immunodeficient condition, including human immunodeficiency virus (HIV) infection, or history of congenital or hereditary immunodeficiency.
9. History of allergic disease or reactions likely to be exacerbated by any component of the vaccine.
10. Acute disease at the time of enrolment. {Acute disease is defined as the presence of a moderate or severe illness with or without fever. All vaccines can be administered to

persons with a minor illness such as diarrhea, mild upper respiratory infection with or without low-grade febrile illness, i.e., temperature  $<38^{\circ}\text{C}$  ( $<100.4^{\circ}\text{F}$ )

11. Acute or chronic, clinically significant pulmonary, cardiovascular, hepatic or renal functional abnormality, as determined by physical examination or laboratory screening tests.
12. Acute or chronic diabetes
13. History of chronic alcohol consumption and/or intravenous drug abuse.
14. Pregnant or lactating female.
15. Female planning to become pregnant.

If a subject signs the consent form but withdraws his/her consent after the 1st injection, he/she will abandon the study as of the date of withdrawal. The subject will attest the withdrawal on the consent form and the reason shall be noted at the end of the CRF. Data collected until the date of withdrawal will be used for the statistical analysis of safety.

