If a subject is lost to follow-up or drops out, this fact shall be noted at the end of the CRF (definitions see 9.1). Data collected for such subjects will be used for the statistical analysis until the date of lost to follow-up or dropout.

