#### 6.4 Dosage and administration

PEV 301 and PEV 302 will be provided in vials. The vials for each group will be provided in individually labeled boxes.

0.5 mL PEV 301 and PEV 302 vaccines should be administered intramuscularly (i.m.) into the deltoid region of the upper arm. The first application is to be given to left, the second to right and the third to the left arm, respectively. The vaccine should not be injected into the blood vessels. The vaccination site should be disinfected with a skin disinfectant (e.g. 70% alcohol) prior to vaccination. The Investigator should use only the needles provided by the Sponsor.

The subjects will be observed closely for at least 30 minutes after vaccination, with appropriate medical treatment readily available in case of a rare anaphylactic reaction following the administration of vaccines. Any reactions that occur during this time must be recorded by the Investigator in the CRF.

The subjects will be instructed to contact the investigator immediately should they manifest any signs or symptoms they perceive as serious. They have to note any signs or symptoms they notice following the vaccinations, on a diary card provided to them.

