**Lost to follow-up:**

From an analysis perspective, a 'lost to follow-up' is any subject who completed all protocol specific procedures up and including to Day 1, including vaccination, but was then lost to any further follow-up, (no safety information and no efficacy endpoint data ever became available)

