**Drop-outs:**

Any subject for whom data is available for at least one follow-up visit but did not complete the study as foreseen in the protocol.

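### Sections 10.9 and 4.3 give different rules for a vaccinated subject whose only safety data are the 30-minute observation

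*Protocol*

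**What the plan says.** Section 10.9 sets two conditions for the safety population: at least one dose of study vaccine or virosomes, "and for whom at least one set of safety follow-up data is available (i.e. safety population". It does not say what makes up a set.

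The closing paragraphs of section 4.3 set no such condition. For a subject who withdraws consent after the first injection: "Data collected until the date of withdrawal will be used for the statistical analysis of safety". For a subject who is lost or drops out: "Data collected for such subjects will be used for the statistical analysis until the date of lost to follow-up or dropout". This second sentence refers to 9.1 for its definitions.

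Section 9.1 defines a lost subject as one who was vaccinated on Day 1 "but was then lost to any further follow-up, (no safety information and no efficacy endpoint data ever became available", and a drop-out as "Any subject for whom data is available for at least one follow-up visit" who did not complete the study.

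Safety data are already collected on the vaccination day. Section 6.4 requires at least 30 minutes of observation and adds: "Any reactions that occur during this time must be recorded by the Investigator in the CRF". The Synopsis lists "assessment by investigator during 30 minutes after each vaccination" among the safety criteria, and section 8.3.1 counts immediate reactions as solicited adverse events.

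**The concern.** Safety is the primary objective (2.1), and section 10.5 justifies groups of 8 by the wish to estimate how often adverse events occur. Who is in the denominator therefore matters, and two sections answer differently for the same subject.

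The subject at issue is injected, observed for 30 minutes, and then withdraws or does not return. Not returning can be related to how the injection was tolerated. A rule that requires a return visit may then remove a subject together with the event observed. In a group of 8 this can be the only event of its type.

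**Working it through.** **1. No planned figure to reproduce.** Section 10.5 gives no formula or expected rate. The group sizes do add up: 5 × 8 + 6 = 46, and 18 + 18 + 10 = 46, as stated.

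**2. What follow-up means in the protocol.**
- Section 3 counts three follow-ups after each vaccination, apart from the vaccination itself.
- Section 5.2.3 describes them as the visits at +2, +7 and about +21 days (it prints 22; the schedule prints 21).
- The Schedule of Assessments separates the first-vaccination visit from the follow-up visits.
- Section 9.1 requires data from a follow-up visit for a drop-out.

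The vaccination-day observation is thus mostly treated as separate from follow-up. No sentence says outright that it does not count.

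**3. The rules side by side.**

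| Dosed subject | 4.3 | 10.9, likelier reading | 9.1 category |
|---|---|---|---|
| Withdraws consent on Day 1 after the 30-minute observation | Data enter the safety analysis | Outside the safety population | Not a drop-out (no follow-up visit) |
| Immediate reaction recorded, never returns | Data used up to loss | Outside | Neither: safety information exists, but no follow-up visit |
| Returns at +2 days, then stops | Data used | Inside | Drop-out |

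The first row is the clearest conflict, because the withdrawal sentence in 4.3 names the safety analysis. The second row shows the gap in 9.1.

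**4. Size, as an illustration.** Assume that one subject in an active group of 8 reacts within 30 minutes and provides nothing afterwards. The documents give no rate for either event. Exact (Clopper-Pearson) 95% limits for x events in n subjects are:

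- lower = 0.025 quantile of Beta(x, n − x + 1), or 0 when x = 0
- upper = 0.975 quantile of Beta(x + 1, n − x); for x = 0 this is 1 − 0.025^(1/n)

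| Situation | All dosed subjects | 10.9, likelier reading |
|---|---|---|
| The lost subject is the only reactor | 1/8 = 12.5% (0.3% to 52.7%) | 0/7 = 0% (0% to 41.0%) |
| The lost subject and one other reacted | 2/8 = 25.0% (3.2% to 65.1%) | 1/7 = 14.3% (0.4% to 57.9%) |
| Only reactor, five active groups pooled | 1/40 = 2.5% (0.1% to 13.2%) | 0/39 = 0% (0% to 9.0%) |

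For 0/7 the upper limit is 1 − 0.025^(1/7) = 41.0%.

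**5. The opposite case.** If the lost subject did not react, 0/8 becomes 0/7, so the estimate stays at 0% and the upper limit moves from 36.9% to 41.0%. With one other reactor, 1/8 = 12.5% becomes 1/7 = 14.3%. The observed rate stays the same or rises.

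**The case against.** The best defence is that the key phrase in 10.9 is undefined and can be read to include the 30-minute record. Section 9.1 speaks of further follow-up, which may imply that follow-up has already begun by the end of Day 1. Section 8.3.1 puts immediate reactions in the same class as those in the four-day period. The schedule places the 30-minute observation in its adverse-event row, and section 10.7.1 assesses safety during the procedure as well as at later visits. On that reading the subject stays in and 10.9 agrees with 4.3. The remark in 9.1 about absent safety information can likewise be read as a condition for being called lost, not as a statement that the 30-minute record does not count.

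The case is also narrow. Section 9.3 asks for attempts to contact non-returners, and a successful contact could supply follow-up data. Anaphylaxis must be followed to resolution (4.4). Adverse event recording (8.2), SAE reporting (8.8) and the DSMB triggers (9.4) do not depend on the safety population. Requiring a dose plus some post-dose safety data is a recognisable definition, and an analysis plan could say what a set is.

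Much of this stands. It rules out three stronger claims that a reader might infer:
- That 10.9 certainly excludes an immediate reactor. The wording is ambiguous.
- That the rule always makes the vaccines look safer. Step 5 of the working shows that it does not when the lost subject had no reaction.
- That a given number of the 46 subjects would be affected. The documents give no loss rate, and counting all early losses would overstate the number who also reacted.

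The defence does not remove the difference between the two sections. The protocol's prevailing use of follow-up favours the exclusion, and an analysis plan that adopted that use would contradict 4.3.

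**Conclusion.** The point holds as a conflict between 10.9 and 4.3 over a vaccinated subject who leaves before the first follow-up visit, with a related gap in 9.1. It rests on reading follow-up in 10.9 as the protocol mostly uses it, which is likely but not certain.

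Its importance is small. It needs a subject to leave on the vaccination day and attempts at contact to fail, and it lowers an observed rate only if that subject also had an immediate reaction. The change from 12.5% to 0% in a group of 8 shows what one such subject would do. It is not a prediction. The harm is to the analysed numerator and denominator, not to safety oversight during the trial. The repair is worth making because the primary analysis is involved and the cost is slight.

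**What to change.** - **10.9:** define the safety population as all subjects who received at least one dose of study vaccine or virosomes, and delete the follow-up condition. State that the 30-minute observation is safety data.
- **Tables:** keep subjects without later data in the denominator for immediate reactions. Show them as missing, with their number, for later windows.
- **9.1:** reword the definitions so that a subject who does not return after the vaccination visit has a category, whether or not a reaction was recorded during the observation.
- **4.3:** make the sentence on lost subjects and drop-outs name the safety analysis, as the withdrawal sentence does, and refer to 10.9.

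The cost is a few sentences. No extra data are needed, since 6.4 already requires the observation and the recording of reactions.

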| PROCEDURE                                  | 
Volunteers will be screened, enrolled and followed by the clinical investigator, PD [name] at the Clinical Research Centre of the Kantonsspital Basel.
 
At the screening-visit (days -7 to -5) and after written informed consent has been obtained, the eligible healthy subjects are randomized to vaccination with either three injections of PEV 301 10 µg (Group A) or PEV 302 10 µg (Group B) or PEV 301 50 µg (Group C) or PEV 302 50 µg (Group D) or PEV 301 50 µg plus PEV 302 50 µg (Group E) or virosomes alone (group F) at days 1(+2), 64(+2) and 183(+2).
 
If possible 23 men and 23 women should be enrolled; however, if it is not possible to have an equal sex distribution, the groups can be filled with participants of either sex.
 
The 18 volunteers recruited in October will first be stratified into males and females and then randomized in blocks of 9 (1 block = females, 1 block = males) into 3 groups: Group A (n= 8) will be vaccinated with 10 µg PEV 301, Group B (n = 8) will be vaccinated with 10µg PEV 302, and 2 volunteers will receive virosomes alone (Group F) 5 weeks later again 18 volunteers have to be recruited, they first will be stratified into males and females and then randomized into 3 groups: group C (n = 8) will be vaccinated with 50 µg PEV 301, group D (n = 8) with 50 µg PEV 302, and 2 volunteers will receive virosomes alone (Group F).
 
5 weeks after the 2nd vaccination of groups C and D 10 volunteers will be randomized in blocks of 5 to either group E (n = 8) receiving the combination of 50 µg PEV 301 plus 50 µg PEV 302 or group F (n = 2) receiving virosomes alone.
 
Immunogenicity assessments for humoral immune response are made at baseline (screening blood sample on days -7 to -5), on the days of the 2nd and 3rd vaccination (pre-vaccination samples) as well as 21 (+5) days after each vaccination.
 
Cell mediated immune response will be assessed in groups C, D, E and F only, at baseline (during screening), and 21 (+5) days after each vaccination.
 
Safety assessments are made by the investigator at baseline (before the 1st immunization) and before the 2nd and 3rd immunization as well as 2 (+1) and 7 (+2) days after each immunization.
 
After each immunization the volunteers have to remain in the clinic for a 30 minutes period for the assessment of local and systemic reactions.
 
The volunteers themselves have to fill an adverse event report form (diary card) for a 4 day observation period after each vaccination. Health status will be checked before each immunization, and on days 21 (+5) 85 (+2) and 204 (+2).
 
Standard blood chemistry and hematology will be assessed at the screening visit (days -7 to -5), prior to each vaccination as well as 7 (+2) and 21 (+5) days after each vaccination.
 |                     |                                                                                                                                                          |                 |                                          |

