 T-cells will not be assessed in groups PEV 301 10 µg and 302 10 µg

a Should be 9 weeks after the 1st vaccination

b must be 2 (+1) days after vaccination

c must be 7 (+2) days after vaccination

d Must be 21 (+5) days after vaccination

e Should be 26 weeks after the 1st vaccination

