## 3 Study Design

This prospective phase I, single centre, randomized, single blind, placebo controlled, dose escalating study will be conducted in 46 healthy adult volunteers. Eligible study participants will be randomized into six groups: PEV 301 10 µg (group A, n = 8) or PEV 302 10 µg (group B, n = 8) or PEV 301 50 µg (group C, n = 8) or PEV 302 50 µg (group D n = 8) or PEV 301 50 µg plus PEV 302 50 µg (group E, n = 8) or virosomes alone (group F, n = 6).

Study participants will be vaccinated three times, i.e. at days 1, 64(+2) and 183(+2) and followed-up 3 times after each vaccination. If any of the study groups does not show any immune response 3 weeks after the 2nd vaccination, no 3rd vaccination will be given to that group, i.e. the study for that group will be terminated 3 weeks after the 2nd vaccination.

Groups C & D (PEV 301 50 µg; PEV 302 50 µg) will be started 5 weeks after the 1st vaccination of groups A, B.

Group E (PEV 301 plus PEV 302) will be started 5 weeks after the 2nd vaccination of groups C and D.

Group F will be distributed and serve as a control in all groups receiving the active product.

The total duration of the study for each participant is 31 weeks, the number of visits is 13.

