## 5 Conduct of study

### 5.1 General study aspects

The clinical part of the study will be conducted at the Clinical Research Centre of the Kantonsspital Basel. PD [name] is the Clinical Investigator.

It is the investigator's responsibility to ensure that the intervals between visits/contacts are strictly followed. These intervals during the active phase of the study determine a subject's evaluability in the as per protocol analyses.

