### 5.2.2 Vaccinations

Volunteers will be vaccinated on days 1, 64 (57 – 66) and 183 (176 – 187) respectively. The 3rd vaccination will not be applied, if 3 weeks after the 2nd vaccination no immune response is seen.

Prior to the vaccination the baseline AE rate has to be assessed by the investigator.

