### 5.2.3 Follow-up visits

For timepoints see schedule of assessments, page 8

Study participants have to report to the study site 48 hours, i.e. on day 2 (+1) after each vaccination. If a visible local reaction occurs, the investigator has to take a picture of the injection site. He has to record any adverse events in the CRF. The investigator has to check whether the study participants fill in the diary card provided to them.

The second follow-up visit has to be performed 7 (+2) days after each vaccination. The investigator has to collect the diary card, to record any adverse events not recorded by the participant and to take blood samples for safety checks (see 5.3.4.)

The 3rd follow-up visit has to be made 22 (+5) days after each vaccination. The investigator has to assess the health status of the participant and to take blood samples for safety and immunology tests (see 5.3.4.)

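### The immunogenicity set in Section 10.9 depends on permitted intervals that the protocol states inconsistently, and its second-dose rule removes valid post-dose-1 samples

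*Protocol*

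**What the plan says.** Section 10.9 defines the per-protocol set for the final immunogenicity analysis, and the protocol defines no other immunogenicity set. Membership requires that "Allowed intervals between injections were respected", that blood-sampling intervals were likewise kept, and that "They received a second dose of the vaccine". No interval is given there. Section 5.1 confirms that the intervals decide membership: "These intervals during the active phase of the study determine a subject's evaluability in the as per protocol analyses".

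The injection windows appear in two versions:
- Section 5.2.2: "Volunteers will be vaccinated on days 1, 64 (57 – 66) and 183 (176 – 187) respectively". The synopsis row on duration and frequency and the study-day row of the Schedule of Assessments agree with this.
- Section 3: "i.e. at days 1, 64(+2) and 183(+2) and followed-up 3 times after each vaccination". The synopsis procedure gives the same days for doses 2 and 3 and adds a +2 tolerance to day 1.

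The third follow-up visit, at which immunology blood is drawn, also has two versions:
- Schedule, footnote d: "Must be 21 (+5) days after vaccination". The synopsis agrees.
- Section 5.2.3: the third "follow-up visit has to be made 22 (+5) days after each vaccination".

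On who contributes data, Section 10.6 analyses each immunological time point separately. The end of Section 4.3 says that data from dropouts are used up to the date of dropout.

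**The concern.** A criterion that decides who is analysed must give one answer per volunteer. Here a volunteer given dose 2 on day 60 is per protocol under Section 5.2.2 and a deviator under Section 3. With eight volunteers per active group, moving one in or out matters. Group-level immune results are also seen at the interim analysis (Section 10.8) before the final set is applied, so the ambiguity could end up being settled with results in view.

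The second-dose rule raises a separate problem. Section 10.6 calls for a post-dose-1 summary, but 10.9 drops any volunteer who stops before dose 2, even with a valid sample after dose 1. That conditions an early measurement on a later event, possibly one related to tolerating dose 1. It also does not sit with the statement in Section 4.3 on using dropouts' data.

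**Working it through.** **Inputs.** Dose windows come from Section 5.2.2 and the Schedule (57-66; 176-187) and from Section 3 (64(+2) = 64-66; 183(+2) = 183-185). Visit offsets come from the Schedule footnotes: 2(+1), 7(+2) and 21(+5) days. Section 5.2.3 gives 22(+5).

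**1. Reproducing the Schedule.** Visit window = [earliest dose day + minimum offset, latest dose day + maximum offset].

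| Visit | Computed | Printed |
|---|---|---|
| Dose 1, 2(+1) | 3-4 | 3-4 |
| Dose 1, 7(+2) | 8-10 | 8-10 |
| Dose 1, 21(+5) | 22-27 | 22-27 |
| Dose 2, 2(+1) | 59-69 | 59-69 |
| Dose 2, 7(+2) | 64-75 | 64-75 |
| Dose 2, 21(+5) | 57+21=78 to 66+26=92 | **78-96** |
| Dose 3, 2(+1) | 178-190 | 178-190 |
| Dose 3, 7(+2) | 176+7=183 to 187+9=196 | **183-197** |
| Dose 3, 21(+5) | 197-213 | 197-213 |

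Two windows do not reproduce. An immunology sample on days 93-96 is inside the printed column but cannot satisfy footnote d for any permitted dose-2 day. The 183-197 visit is a safety visit without immunology blood. It matters here only if the sampling criterion in 10.9 is meant to cover every blood draw, which 10.9 does not say.

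**2. Injection windows.**
- Dose 2: 57-66 has 10 days and 64-66 has 3. They disagree on 57-63, which is 7 of 10.
- Dose 3: 176-187 has 12 days and 183-185 has 3. They disagree on 176-182, 186 and 187, which is 9 of 12.
- If the plus sign is a lost plus-or-minus (an assumption), the narrow windows become 62-66 and 181-185. Disagreement remains on 5 of 10 and 7 of 12 days.

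**3. As intervals between injections, the term 10.9 uses.** Dose 2 to dose 3 is 176-66 = 110 to 187-57 = 130 days under the Schedule, but 183-66 = 117 to 185-64 = 121 days under Section 3.

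**4. Sampling.** 21(+5) allows days 21-26 after vaccination and 22(+5) allows 22-27. They disagree on days 21 and 27.

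**5. Second-dose rule.** Take a volunteer with a valid sample after dose 1 who drops out before dose 2. Section 4.3 uses the data up to dropout, Section 10.6 has a summary for that time point, and Section 10.9 excludes the volunteer. A volunteer barred from further doses under Section 4.4 who stays for other procedures is excluded in the same way. Section 4.3 limits data to the safety analysis only for volunteers who withdraw consent after the first injection, so it does not resolve the other cases.

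**6. Sensitivity with 8 per group (illustration).** Two responders among 8 is 25%. If two non-responders fall outside a window, 2 of 6 is 33%. Section 10.4 speaks of at least one third of volunteers; applying that per group is an assumption.

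**The case against.** The protocol largely signals which table to use. Section 4.4 sends postponed injections to the Schedule's window, and Section 5.2 refers to the Schedule for the timing of visits and vaccinations. The Schedule, Section 5.2.2 and one synopsis row agree. That carries weight, but it does not settle the matter. Nothing says the Schedule overrides Section 3 or the synopsis procedure, 10.9 does not cite it, and the Schedule departs from its own footnotes twice. The 22(+5) may be a slip from the Schedule's study days 22-27, and it shifts the window by only one day at each end.

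A single set with a two-dose minimum keeps the same volunteers in every summary and suits a design in which a group may stop after dose 2 (Section 10.8). That explains the rule, but it does not reconcile it with Section 4.3 for post-dose-1 samples.

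Three stronger readings are tempting but not supported:
- **The conflict leaves fewer than the 34 evaluable volunteers sought.** The documents give no distribution of dosing days. Footnotes a and e aim at 9 and 26 weeks, which are days 64 and 183 and lie in both versions. Section 10.9 requires only a second dose.
- **The set is wrong for the post-dose-3 summary because a third dose is not required.** Footnote d ties that sample to a vaccination, so a volunteer without dose 3 would ordinarily have no qualifying sample. The concern there is marginal.
- **Days 85(+2) and 204(+2) in the synopsis procedure are another sampling conflict.** They belong to health-status checks, not immunology sampling.

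**Conclusion.** The point holds. The permitted intervals decide membership of the only immunogenicity set defined, and they are stated inconsistently for dose 2, dose 3 and the immunology visit. Seven of 10 dose-2 days and nine of 12 dose-3 days change status with the section read. These counts are exact day arithmetic. The number of volunteers affected cannot be computed, because neither timing nor dropout rates are given.

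The second-dose requirement is at odds with Sections 4.3 and 10.6 for post-dose-1 data.

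The consequence is moderate. The safety population does not use these intervals. Immunogenicity is a secondary objective, mainly descriptive, and Section 10.5 says the study is not powered for differences between regimens. A reader might infer that windows would be chosen to suit the titres. The text leaves room for that but gives no sign of it.

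**What to change.** Reconcile the synopsis (duration row, immunogenicity timing and procedure), Section 3, Sections 5.2.2 and 5.2.3, and the Schedule with its footnotes to one window per injection and per visit, including the 78-96 and 183-197 columns. Which window applies is for the sponsor and investigator to decide; none is preferred here. Have Section 10.9 cite that single table, and say which blood samples its sampling criterion covers, before titres are known.

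Replace the blanket second-dose requirement with a rule for each time point: the volunteer received all injections scheduled before that sample. This keeps valid post-dose-1 samples and brings 10.9 into line with Sections 4.3 and 10.6.

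The cost is wording changes to the protocol, carried through to any analysis plan. No new data, visits or volunteers are needed.
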